### Spirometry measurements

Lung function data will be collected in the seated position using a Koko Legend spirometer (CareFusion, Toronto, Canada) before and after administration of 400 μg of the inhaled bronchodilator salbutamol via a metered-dose inhaler with a spacer, following American Thoracic Society (ATS) standards [26]. Each measure will be reviewed by a board-certified respirologist (co-authors [name]) who will be blinded to details of medical history and risk factors. The presence of a ratio of post-bronchodilator forced expiratory volume in the first second (FEV_1_) to forced vital capacity (FVC) < 0.70 will be used to determine airflow obstruction consistent with COPD. The severity of COPD will be categorized according to the GOLD guidelines [3]. There are no validated prediction equations for First Nations populations, therefore we will use Canadian prediction equations of lung function [27] which are similar to the widely-used equations in the U.S. National Health and Nutrition Examination Survey [28]. The respirologist will also make note of any other lung function abnormalities (e.g., evidence of asthma or interstitial lung disease) that require follow-up by the family physician.

### Lung health questionnaires

Each participant will complete the American Thoracic Society Epidemiological Respiratory Questionnaire [29] with additional items from the Saskatchewan First Nations Lung Health Study [11] questionnaire as well as items related to relevant occupational, environmental, and cultural exposures. These extensive questionnaires contain detailed questions related to smoking history (cigarette, marijuana, vaping, and other smoked products), childhood and family history of lung disease, respiratory symptoms, comorbid conditions, other inhaled risk factors, residential air quality, outdoor air quality,, medication use, health care utilization (HCU), activity limitation, occupational history and exposures, time spent in household and community buildings, financial security, community strengths, residential school attendance and self-report of discrimination. The additional questions were developed in consultation with the Community Research Advisory Committee, and include Indigenous perspectives in maintaining one’s own health by asking: What do you do to keep your lungs healthy? If you have problems with your breathing, what do you do to get better? What are the strengths of your community?

### Previous physician diagnosis of COPD

CSFS provides primary health services to all residents living on reserve. Care provided by family physicians, nurse practitioners, nurses and other health care professionals is detailed in the CSFS electronic health record (EHR). Participants who allow access of their EHR will be categorized as having physician-diagnosed COPD if any of the following occur in their medical records: 1) COPD, chronic obstructive lung disease, chronic airflow limitation, chronic bronchitis, or emphysema in the diagnosis fields; 2) history of an acute exacerbation of COPD (AECOPD) with or without hospitalization; or 3) six or more consecutive months of the COPD-specific long-acting bronchodilator tiotropium bromide prescribed without a diagnosis of asthma and 10 or more pack years of cigarette smoking.

### Health care utilization

Using the EHR system, we will count the number of respiratory-related visits in the previous 2 years to the primary care physician, nurses, and nurse practitioners. Eligible respiratory-related events will include lower respiratory tract infections, bronchitis, shortness of breath, and productive cough. We will also ask participants how many times they visited any Emergency Department and/or were admitted to any hospital for respiratory-related problems in the previous year.

### Household and community measures of air quality

We will measure air quality in occupied residences and community buildings (including health centres, Band offices, and community centres). The major sources of indoor air pollution are combustion products (second-hand smoke, wood burning) and pollutants related to excess moisture in interior structures and furnishings. We will collect data via direct observations and physical samples. Participants also consent to the home inspection visits and sampling of household indoor air. We will get permission to sample community buildings from Chief and Council. We will also meet with Chief and Council to determine the appropriate manner of reporting air quality findings back to each community.

A standard unit of extracted dust will be analyzed using enzyme-linked immunosorbent assay (ELISA) reagents obtained from Indoor Biotechnologies (https://inbio.com) and read on a Molecular Devices SpectraMax 190 microplate reader. The following compounds will be examined from the same house dust sample: antigens (housedust mite Der p1 and Der f1; cat Fel d1; dog Can f1; mouse Mus m1) and mould antigens (*Alternaria alternata* Alt a1; *Aspergillus fumigatus* Asp f1). The limit of detection of ELISA antigen determination is 0.4 ng/mL extract. The pro-inflammatory molecule, endotoxin, will be quantified using a kinetic, chromogenic reaction using Limulus Amoebocyte Lysate (LAL) reagent (Kinetic QCL, Lonza Walkersville Inc.). Samples will be also stored as baseline measures for remediation studies.

### Data analysis

Using pooled data, descriptive statistics will be used to characterize participants and their communities, including lung function, symptoms, HCU and risk factors. The prevalence of COPD will be calculated as the ratio of COPD cases, based on lung function, to the sampled population. To get a representative estimate of the population prevalence of COPD in remote and rural First Nations communities in BC, we will consider the cluster design and sampling weight, which is the inverse of the likelihood of being sampled. The sampling weights in this study will be computed as the ratio of household size to total population in each community. These weights will be included in the calculation of prevalence with 95% confidence interval estimation. Under-diagnosis of COPD will be estimated by confirming the prevalence of COPD based on spirometry with the medical diagnosis in the EHR.

Secondary analyses will estimate the levels of indoor air pollutants and compare them to consensus guidelines established by the American Society of Heating, Refrigeration and Air-Conditioning Engineers [33, 34] and Health Canada [35]. We will characterize the levels of inhaled pollutants from individual, residential, occupational, cultural/community sources as well as respiratory symptoms, airflow obstruction, and respiratory-related HCU.

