## Methods

The research team is a longstanding partnership between researchers at the University of British Columbia (UBC), the participating First Nations, and Carrier Sekani Family Services (CSFS) – the latter being an organization that provides direct health and social services to First Nations communities in North-Central BC. Community involvement was achieved as the study concept and design was reviewed, revised, and approved by the CSFS Community Advisory Board which is made up of a representative member of the public from each participating First Nation. Research projects undertaken with CSFS require this approval from and engagement with the CSFS Community Advisory Board, which ensures study processes are supported by CSFS, data is owned by the community, and all research provides tangible benefits to the First Nations communities. This decolonizing methodology [22] is mandated in Chapter 9 of the *Tri-Council Policy Statement*, titled “Research Involving the First Nations, Inuit and Métis Peoples of Canada” [23], and forms part of our approved ethics review for this study.

This study will recruit adults 30 years and older from 11 First Nations communities in remote and rural locations in northern British Columbia. The study will consist of detailed questionnaires, lung function measurement, air quality sampling, building assessments, and community-engagement activities. Each eligible adult within a randomly-selected household will be invited to participate and provide informed consent. Data collection will occur between September to April in the 2017–2023 study period in order to obtain air quality measures during high occupancy periods and when indoor heating is likely to occur.

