### Sample size and household/individual sampling

We used the Statistics Canada 2016 Census [24], the First Nations Profile [25] and the CSFS community registry to determine our estimated target population to be 1600 adults age 30+ years living in the 11 First Nations. Assuming the prevalence is 13%, a sample size of 220 adults from a population of ~ 1600 would result in a 95% confidence interval of prevalence with a half width no more than 0.05 if the intra-cluster correlation is ≤0.25. This estimate takes into account the fact that household residents are likely to be related meaning that each participant is not independent. On average, there are 2–3 adults per First Nations household [6], therefore approximately 88 households will be needed. We have planned for an additional 20% more households to ensure enough participants.

We will recruit a specific number of people from each community, which will be proportional to the adult population contribution of that community to all the CSFS communities. We estimate that we will be able to recruit 1–2 adults per household. Using a random-number generator, each household is then randomly placed in numbered order. Starting at the top of the list, we then approach the adults in that household with an invitation to participate. If that household declines, we move to the next household on the list. Based on previous Canadian COPD prevalence studies using random population sampling and direct measures of lung function [3, 18, 19], the prevalence of COPD in Canada is 8.1% among all adults, and 15% among ever-smokers. Due to the high prevalence of smoking in First Nations communities, the true prevalence of COPD is likely greater than 8%, so we have used 13% as our estimate for sample size calculations.

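### The analysis section claims a prevalence representative of remote and rural First Nations communities in BC, but the frame, weights and precision statement cover only the 11 participating Nations

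*Protocol article*

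**What the plan says.** The protocol article describes the population in several ways.

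- **Methods, opening text:** recruitment is from "11 First Nations communities in remote and rural locations in northern British Columbia". The partner organisation provides health and social services in north-central BC.
- **Sample size and household/individual sampling:** census, profile and registry data are used to put "our estimated target population to be 1600 adults age 30+ years living in the 11 First Nations". The precision statement is tied to that number: "a sample size of 220 adults from a population of ~ 1600 would result in a 95% confidence interval of prevalence". Its half-width is to be at most 0.05, at an assumed prevalence of 13% and an intra-cluster correlation of up to 0.25. The stated reason for allowing for clustering is that "household residents are likely to be related meaning that each participant is not independent". Each community's share of the sample is proportional to its adult population, and households are put in random order.
- **Data analysis:** clustering and weights are considered "To get a representative estimate of the population prevalence of COPD in remote and rural First Nations communities in BC". The weights come from household size and the total population of each community.
- **Elsewhere:** the Abstract and the end of the Background speak of several communities in BC. The closing paragraph of the Discussion speaks of communities in northern BC.

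**The concern.** The sample size section and the analysis section name different populations. The first is a closed list of 11 Nations with about 1600 eligible adults. The second, read as written, is the wider set of remote and rural First Nations communities in the province, and weighting and clustering are offered as the means of representing it.

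They cannot do that. An inverse-probability weight exists only for units that could have been selected. As described, randomisation operates on households within participating communities, so communities outside the 11 had no chance of selection.

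The two populations also call for different standard errors. A finite population correction for 1600 adults is proper for the 11 Nations. For a wider population it would not apply, and variation between communities would have to be added, estimated from only 11 of them.

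The Background gives a reason not to treat the region as interchangeable with the rest of BC. It reports heavier household wood burning in the north than elsewhere in the province, frequent forest fires, and a link between such exposure and respiratory symptoms. The results are meant for health authorities and service planning, so the population attached to the interval matters.

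**Working it through.** **Inputs, all from the sample size section.** Prevalence p = 0.13; n = 220; N ≈ 1600; intra-cluster correlation (ICC) 0.25; 88 households, so m = 220/88 = 2.5 adults per household. The section gives 2–3 adults per household on average, but expects to recruit 1–2.

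**Formulas.**
- Design effect: DEFF = 1 + (m − 1) × ICC
- Finite population correction (FPC): (N − n)/(N − 1) = 1380/1599 = 0.863, square root 0.929
- Half-width: 1.96 × √[p(1 − p)/n × DEFF × FPC]

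**Step 1: reproduce the plan's figure.** At m = 2.5, DEFF = 1 + 1.5 × 0.25 = 1.375.
- Without FPC: 1.96 × √(0.1131/220 × 1.375) = 0.0521
- With FPC: 0.0521 × 0.929 = 0.0484, which meets 0.05

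In the other direction, a simple random sample for a half-width of 0.05 needs 1.96² × 0.1131/0.05² ≈ 173.8. With the correction this is 173.8/(1 + 172.8/1600) ≈ 156.9, and multiplied by 1.375 it is 215.7, or 216 against the stated 220. The plan's figure is therefore reproduced with the correction. Without it, 173.8 × 1.375 ≈ 239.0, or 239 adults.

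**Step 2: vary the cluster size.**

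| Adults per household | DEFF | Half-width with FPC | Half-width without FPC |
|---|---|---|---|
| 1.5 | 1.125 | 0.0438 | 0.0471 |
| 2 | 1.25 | 0.0462 | 0.0497 |
| 2.5 | 1.375 | 0.0484 | 0.0521 |
| 3 | 1.5 | 0.0506 | 0.0544 |

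Of these sizes, only at 2.5 does the correction decide whether 0.05 is met. At 2 or fewer it is met either way; at 3 it is missed either way. At m = 2.5 the largest ICC compatible with 0.05 is 0.311 with the correction and 0.177 without.

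**Step 3: between-community variance, illustration only.** The article gives no community-level ICC. Assume 0.005 to 0.05, with 220/11 = 20 adults per community, no FPC and m = 2.5. The design effect becomes 1.375 + (20 − 2.5) × ICC of the community, that is 1.4625 to 2.25. The half-width is then 0.054 to 0.067 with the normal quantile, or 0.061 to 0.076 with a t quantile on 10 degrees of freedom. This variance enters only for the wider target. If the 11 Nations are the whole target, they are all in the sample and act as strata.

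**Step 4: what the weights can reach.** They are built from household size and the population of each sampled community. No term refers to a community outside the 11, so the weighted total can represent at most the adults of those 11.

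**The case against.** The strongest reply is that the sentence is shorthand. The target is fixed in the sample size section, and the Abstract and Background are suitably narrow. The 11 communities are themselves remote and rural and lie in BC. The title uses the same phrase with Canada as a plain locator. The next lines of the analysis section build weights from the participating communities only, so the planned calculation already concerns them.

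Much of this stands. A reader might infer that the study is set to compute an interval for a population it did not sample. The documents do not support that: the computation described is for the 11 Nations, and the label is what goes too far. But the wide label sits in the sentence that states the purpose of the weighted estimate and its interval, and the article's scope wording differs between sections, so it should not be left for readers to interpret.

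A reader might also infer that the 0.05 target is already missed for any population beyond the 1600. That does not hold either. At two per household, the upper end of the expected recruitment, the uncorrected half-width is 0.0497. At three, the target is missed even for the 11 Nations (0.0506), which says nothing about scope. At 2.5 the shift is 0.0521 − 0.0484 = 0.0037, under 0.4 percentage points.

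It is also fair to say that the correction is never named, that any between-community figure is assumed, and that the variance estimator may be set out in a fuller document.

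**Conclusion.** The point holds as one of scope. The analysis section names a wider population than the frame, the weights and the precision statement support, and weighting cannot close that gap. This conclusion does not depend on cluster size.

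The numerical consequence is modest and conditional. At 88 households, 2.5 adults each and ICC 0.25, the 0.05 half-width is met for the 11 Nations (0.0484) and not without the finite population correction (0.0521). At two or fewer participants per household it is met in both cases, before any between-community variance.

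Three assumptions remain:
- Use of the correction is inferred from the reference to a population of about 1600 and from the reproduction of n (216 against 220).
- The absence of community sampling is read from the account of participating partner Nations and of household randomisation.
- The community-level ICC range of 0.005 to 0.05 is illustrative and has no source in the article.

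**What to change.** In the Data analysis section, state the target as *the prevalence of COPD among adults aged 30 and over living in the 11 participating First Nations*, and use the same population wherever the article states what the estimate represents.

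Treat the 11 communities as strata, in line with the fixed proportional allocation, with households as clusters, and apply the finite population correction explicitly. State that any extension to other First Nations communities in BC is a judgement not covered by the confidence interval.

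The cost is a few sentences and a narrower claim. The sample size of 220 does not change.

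### The stated sampling weight, household size over community population, is not the inverse selection probability that the plan itself defines, and it gives each Nation about equal weight whatever its size

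*Protocol article*

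**What the plan says.** All references are to the protocol article.

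- **Definition of the weight (Data analysis).** The plan will take account of clustering and of the "sampling weight, which is the inverse of the likelihood of being sampled".
- **Formula (next sentence of the same section).** "The sampling weights in this study will be computed as the ratio of household size to total population in each community".
- **Use.** "These weights will be included in the calculation of prevalence with 95% confidence interval estimation". The weights therefore enter the primary estimate.
- **Household selection (Sample size and household/individual sampling).** "Using a random-number generator, each household is then randomly placed in numbered order". Households are approached from the top of the list, and one that declines is replaced by the next.
- **Selection within the household (Methods).** "Each eligible adult within a randomly-selected household will be invited to participate and provide informed consent".
- **Allocation to communities (Sample size and household/individual sampling).** The number recruited in each community is "proportional to the adult population contribution of that community to all the CSFS communities".
- **Expected yield (same section).** "On average, there are 2–3 adults per First Nations household", but "We estimate that we will be able to recruit 1–2 adults per household".

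**The concern.** Two adjacent sentences disagree. The first gives the correct principle. The second gives a quantity below 1 that looks like a selection probability (one draw with chance proportional to household size) and does not invert it. The design described elsewhere does not draw households in proportion to their size either.

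Prevalence is the purpose of the study, and the results are meant to support planning of health services. The weights are there to make the estimate representative of about 1600 adults aged 30 or over. An analyst who follows the formula literally would move the estimate towards small communities and, depending on uptake, towards large households. The analyst would also add variance for which the sample size makes no allowance.

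**Working it through.** **1. The plan's own precision figure.** Inputs from the sample size section: prevalence p = 0.13, n = 220, N = 1600, intra-cluster correlation 0.25, about 88 households, hence 220/88 = 2.5 participants per household.

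- Design effect = 1 + (2.5 − 1) × 0.25 = 1.375.
- Half-width = 1.96 × √(0.13 × 0.87 / 220 × 1.375) × √(1380/1599) = 0.0484.

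The stated limit of 0.05 is reproduced and is not in dispute. It contains no term for unequal weights.

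**2. Weights implied by the design.** Let community c have H_c listed households, of which k_c are reached, and N_c adults. Let a household have m eligible adults, of whom a take part.

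- If all adults take part, the selection probability is k_c/H_c, whatever m is. With proportional quotas it is about 220/1600 = 0.1375 everywhere, so the weight is about 7.27 for everyone.
- If only a of m take part, the weight is (H_c/k_c) × (m/a).

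Neither equals m/N_c. Inverting the formula to N_c/m does not repair it: that counts community size twice and favours small households. Reading household size as the number of households in the community would give nearly equal weights by accident, but still not an inverse probability.

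**3. Effect of dividing by community population.** The weights in one community sum to n_c × mean(m)/N_c. Because n_c = 0.1375 × N_c, N_c cancels. With mean(m) = 2.5, a community of 400 gives 55 × 2.5/400 = 0.344 and a community of 40 gives 5.5 × 2.5/40 = 0.344. Each of the 11 Nations therefore carries about 1/11 = 9.1% of the weight.

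Illustration with assumed sizes 400, 300, 220, 180, 140, 110, 80, 60, 50, 35 and 25 (sum 1600). Assumed community prevalence: logit p_c = ln(0.13/0.87) ± 0.4 × ln(N_c/145).

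| Assumed pattern | True (weighted by N_c) | Equal weight per Nation |
|---|---|---|
| Prevalence rises with size | 14.7% | 12.0% |
| Prevalence falls with size | 12.0% | 15.1% |
| No relation | 13.0% | 13.0% |

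**4. Effect of the household-size factor alone.** Assumed: households of 1, 2, 3 and 4 adults in proportions 0.20, 0.35, 0.25 and 0.20, with prevalence 20%, 16%, 12% and 9%. The true prevalence is Σ(q·m·p)/Σ(q·m) = 0.314/2.45 = 12.8%.

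| Uptake | Weight proportional to m | Equal weights |
|---|---|---|
| All adults | 0.822/7.05 = 11.7% | 0.314/2.45 = 12.8% |
| At most two | 0.588/4.70 = 12.5% | 0.248/1.80 = 13.8% |
| One adult | 0.314/2.45 = 12.8% | 0.144/1.00 = 14.4% |

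The factor does harm at full uptake and is correct when one adult is recruited per household.

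**5. Precision.** The Kish factor, n·Σw²/(Σw)², multiplies the variance. Assumed community sizes of 80–240 and 40–330, with the household mix above, give about 1.25 and 1.7.

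| Participants per household | Design effect | Kish 1 | Kish 1.25 | Kish 1.7 |
|---|---|---|---|---|
| 2.5 | 1.375 | 0.048 | 0.054 | 0.063 |
| 1.5 | 1.125 | 0.044 | 0.049 | 0.057 |

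The 0.05 target tolerates a factor of (0.05/0.0484)² = 1.07 at 2.5 per household and (0.05/0.0438)² = 1.30 at 1.5. The more uneven sizes in step 3, simulated with households of 1–5 adults, gave factors of about 2.2 to 2.5.

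**The case against.** The strongest reply is that the governing definition is correct and household size does belong in the weight. The plan expects one or two recruits from households with two or three adults, so an eligible-over-participating factor is needed. In the one-adult row of step 4 the stated factor is exactly right, and equal weights are off by 1.6 points. This stands. A reader might infer that the correct weights are simply all equal, but that holds only with full uptake. The reply does not rescue the division by community population, which conflicts with the proportional quotas at any uptake.

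Three other strong readings are tempting and are not supported.

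- **That the prevalence will certainly be wrong.** If prevalence is unrelated to community or household size, the stated weights give 13.0% against a true 13.0%. The article reports no such gradient.
- **That the interval will exceed ±0.05.** At 1.5 participants per household and a Kish factor of 1.25 it is 0.049.
- **That the denominator wrongly counts all residents instead of adults aged 30 or over.** The article also calls the 1600 adults its population, so the term may mean the adult total. If the adult share is similar across communities, the difference largely cancels.

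The same section also describes prevalence as a plain ratio of cases to those sampled. With high uptake that ratio would be nearly unbiased, because the design is then almost self-weighting. But the weighted figure is the one offered as representative.

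Condensation of a fuller protocol is no answer. Nothing is missing here: an explicit formula conflicts with the sentence before it.

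**Conclusion.** The point holds in this form. The formula contradicts the plan's own definition and does not follow from its sampling design. The certain consequence is that, under proportional quotas, each Nation gets about equal total weight whatever its size. Over-weighting of large households follows if most eligible adults take part, and fades as recruitment approaches a fixed number per household.

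Whether the estimate is biased depends on whether COPD prevalence varies with community size, or with household size under high uptake. Under the assumed gradients in step 3 the error is about 3 percentage points in either direction; with no gradient it is nil and the cost is precision. The half-width is 0.049 to 0.063 over the assumed Kish factors of 1.25 to 1.7 and 1.5 to 2.5 participants per household, against a target of 0.05. These figures rest on assumed community sizes, household sizes and prevalence patterns, because the article gives no community sizes. The contradiction itself rests on no assumption. It concerns the primary estimator and should be corrected before analysis.

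**What to change.** Replace the formula sentence with the following: each participant's weight is (households on the community list / households reached on that list) × (eligible adults aged 30 or over in the household / adults in that household with usable spirometry), scaled so that the weights in each community sum to its count of adults aged 30 or over. Use community as the stratum and household as the cluster in the variance.

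The second factor covers partial uptake within households. The scaling absorbs households that decline.

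The cost is one sentence in the analysis section or the statistical analysis plan. The inputs (list length, households reached, eligible adults per household) arise during recruitment, so the study team needs to confirm that they are being recorded. No change to sampling or sample size is required.
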